### Data collection

2.14

The baseline characteristics and follow-up data will be collected by experienced and practiced assessors. The data collection form and the plan are shown in Table 1. Their family members will help them if they have difficulties in completing the evaluation. Any adverse events occurring during the study period are documented. Paper-based or electronic data will be recorded in the data collection form in time.

### Data and safety monitoring

2.15

An independent data monitoring committee (DMC), including physicians, statisticians, and data analysts, will monitor the safety and efficacy of this trial and identify if there is a need to make adjustments. Members of the DMC will assess the trial once a month to review the study data.

### Statistics analysis

2.16

All data are analyzed using the statistical software program SPSS version 19 (IBM, Armonk, NY). Probability values (*P*) less than .05 is considered to have statistical difference. Categorical variables are statistically descried as number (percent). Normal-distribution quantitative data are statistically described as arithmetic mean ± standard deviation (SD) and to compare the difference between the 2 groups, independent samples *t-*test is used. To compare the 2 groups on the data which followed non-normal distribution and are statistically described as median (range), Wilcoxon rank sum test is used. Chi-squared test is used to compare the 2 groups on categorical variables (Fisher's exact test is used while appropriate). Shunt-success rate curve is obtained using the method of Kaplan–Meier and log-rank test is used to compare the difference between the 2 groups.

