### Inclusion criteria

2.4

1.Adult (Age >=18 years);2.Evans index > 0.3;3.Onset secondary to subarachnoid hemorrhage, intraventricular hemorrhage or intraparenchymal hemorrhage;4.non-obstructive hydrocephalus;5.The communication of the ventricles with the spinal subarachnoid space is evident through lumbar puncture and CSF opening pressure is 70-200 mmH_2_O.

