### Sample size

2.6

Previously published reports indicated that the rate of VPS failure is around 15.0% for adult patients with PHH, compared with a rate of 35.0% for LPS cohorts according to our previous study.^[11–14]^ We calculate that a sample of 70 will be required in this clinical trial with a significance level of 5% (2-sided) and a power of 80% to demonstrate a 20% difference in rate of shunt failure. Considering about the loss to follow-up, the sample size is enlarged to 75 for each group.

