### Secondary outcomes

2.13

The secondary outcomes include NIHSS, CGS, mRS, and Evans index at the time of discharge, 3 and 6 months after shunt surgery. A favorable outcome is defined as shunt success with an improvement of more than 1 point in the NIHSS at the evaluation point. Evans index is tested thorough axial CT scan. Complication events throughout the study within 6 months after shunt implantation is investigated. Complication events occurring at any time within 6 months after cranioplasty are investigated.

SAEs occurring at any time is recorded to determine the safety, which is defined as death, an event that could lead to death, an event that require hospitalization or an extension of the hospitalization period, or disability, which is related to the treatment.

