## Discussion

3

With the advent of silastic tubing and programmable pressure valve, CSF shunts diverting the accumulated CSF to the peritoneal cavity remained the standard treatment.^[17,18]^ The most common used type of shunt was VPS while LPS emerged as an effective alternative treatment in 1950s.^[19]^ While an unacceptably higher incidence of shunt failure in the treatment of INPH was observed, few studies tested the benefits of LPS surgery in the treatment of PHH. A retrospective study recently indicated patients with PHH treated by LPS and VPS obtained equal clinical outcomes.^[2]^ However, the best treatment still remains controversial.^[20]^ In this regard, we conducted a prospective, randomized controlled trial to compare the safety and efficacy of VPS cohort with that of LPS cohort with PHH. The primary outcome is the rate of shunt failure 6 months after shunt surgery. The secondary measure of efficacy is the improvement of symptoms and ventricular size, and the incidence of complications at the evaluation point within 6 months. To better of our knowledge, the current study is the first randomized controlled trial that compares the long-term outcomes of VPS with that of LPS in the treatment of PHH. The results of this trial will provide evidence for the optimal treatment options for patients with PHH and may generate the discussion about the optimal treatment. Despite of the strengths, there are still some questions that need to be discussed.

First, the indication and contraindication of LPS implantation remains controversial since the lack of broad consensus and standardized criteria.^[10,11]^ Diverting the accumulated CSF from spinal subarachnoid space to peritoneal cavity, LPS is only suitable and effective for non-obstructive hydrocephalus. In this light, participants those who are suspected for obstructive hydrocephalus based on brain imaging would be excluded from this trial.

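### Secondary scales are compared by tests that do not adjust for the pre-surgery score, in groups formed without randomization, and the NIHSS responder endpoint is out of reach for patients entering at 0 or 1

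*Protocol article*

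**What the plan says.** **Outcomes.** Section 2.13 lists scales by visit: "The secondary outcomes include NIHSS, CGS, mRS, and Evans index at the time of discharge, 3 and 6 months after shunt surgery" (CGS is evidently GCS). It then defines a responder endpoint: "A favorable outcome is defined as shunt success with an improvement of more than 1 point in the NIHSS at the evaluation point". The reference value for that improvement is not named; I read it as the pre-surgery score.

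**Tests.** Section 2.16 sorts tests by type of data. For normally distributed quantities the text reads "to compare the difference between the 2 groups, independent samples" *t*-test. Other quantities get the Wilcoxon rank sum test, categorical variables chi-squared or Fisher, and the shunt-success curve the log-rank test. No covariate, change score or model appears.

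**Timing and allocation.** Sections 2.2 and 2.11 place an assessment before surgery for every participant. Section 2.7 has the patient or an administrator choose the group.

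**Discussion.** The secondary measure is described differently there: "The secondary measure of efficacy is the improvement of symptoms and ventricular size".

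**Eligibility.** The inclusion list begins "Adult (Age >=18 years);2.Evans index > 0.3;3.Onset secondary to subarachnoid hemorrhage" and continues with non-obstructive type and CSF opening pressure. Neither the inclusion nor the exclusion criteria set a minimum NIHSS.

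**The concern.** Without randomization there is no reason to expect equal pre-surgery scores in the two groups. If a patient's later score depends on the earlier one, an unadjusted comparison at follow-up partly shows who chose, or was given, which shunt. The information needed to reduce this is already collected but does not enter the named tests. Precision is lost as well.

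The favorable outcome has a further problem. On an integer scale, a gain of more than 1 point means at least 2. With a lowest score of 0, a patient entering at 0 or 1 is a non-responder however well the shunt works. If the groups differ in their share of such patients, the responder rates differ with no treatment effect. If the shares are equal, the endpoint loses power.

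Symptoms, ventricular size and favorable outcome are what the trial would report beyond shunt failure, so the reading of its secondary results depends on this.

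**Working it through.** **1. The plan's own figure.** The only planned number is for the primary outcome. The inputs from section 2.6 are "the rate of VPS failure is around 15.0% for adult patients with PHH", 35% for LPS, and "a power of 80% to demonstrate a 20% difference in rate of shunt failure", at a two-sided 5% level.

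n = (1.960 + 0.842)² × (0.15×0.85 + 0.35×0.65) / 0.20² = 7.849 × 0.355 / 0.04 = 69.66, rounded up to 70 per group.

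The stated 70 reproduces. It concerns shunt failure only and is not affected by this point. I use 70 (before the loss allowance) and 75 (recruited) as group sizes below.

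**2. Imbalance carried into follow-up scores.** The documents give no SD, no pre/post correlation *r* and no expected imbalance *d*, so all three are assumed. Scores have SD 1 within each group at both times, and there is no treatment effect.

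- Bias at follow-up = r × d.
- Noncentrality of the two-sample *t*-test = r × d × √(70/2) = r × d × 5.916, with 138 degrees of freedom.

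| d (SD) | r | Bias (SD) | Noncentrality | Rejection rate |
|---|---|---|---|---|
| 0.1 | 0.6 | 0.06 | 0.35 | about 6% |
| 0.3 | 0.3 | 0.09 | 0.53 | about 8% |
| 0.3 | 0.5 | 0.15 | 0.89 | about 14% |
| 0.3 | 0.6 | 0.18 | 1.06 | about 18% |
| 0.3 | 0.8 | 0.24 | 1.42 | about 29% |

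The nominal rate is 5%.

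**3. Precision.** Adjusting for the pre-surgery score multiplies the residual variance by 1 − r². With 70 per group and a true difference of 0.4 SD (assumed, normal approximation), power is 65.8% on unadjusted follow-up scores. With adjustment it is 69.9% (r = 0.3), 78.0% (r = 0.5) and 97.6% (r = 0.8).

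Change scores are not an equal substitute. Their variance is 2(1 − r), so at r = 0.3 power falls to 51.6%, below the unadjusted comparison. Their bias under the model of step 2 is (r − 1) × d. With d = 0.3 and r = 0.6 that is −0.12 SD: opposite in sign and not zero.

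**4. The NIHSS floor.** The responder rate is (1 − f) × q, where f is the share entering at NIHSS 0–1 and q the response rate among the others. Take q = 0.5 in both groups, so no true effect. Rejection is by the uncorrected chi-squared test, computed exactly.

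| f, one group vs the other | Responder rates | 70 per group | 75 per group |
|---|---|---|---|
| 10% vs 20% | 45% vs 40% | about 9% | about 10% |
| 10% vs 30% | 45% vs 35% | about 22% | about 25% |

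With equal shares the rates are equal and rejection stays near 5%, but power is lost. Suppose 60% and 40% respond among those able to, with 70 per group. Power is 66% at f = 0, 57% at f = 10% (54% vs 36%), 49% at f = 20% (48% vs 32%) and 41% at f = 30% (42% vs 28%).

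**The case against.** **Baseline is not ignored throughout.** A reader might infer that every secondary analysis disregards the pre-surgery score. That is too strong. The favorable outcome is defined by improvement, so it uses an earlier score; only its test is unadjusted.

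**Comparison of raw scores is inferred.** Section 2.16 never says whether a score or a change enters the *t* or Wilcoxon test, and the Discussion's mention of improvement would fit a test on change. Reading sections 2.13 and 2.16 together, raw scores at visits are the natural meaning, but the text does not say so. This objection stands, which is why the sections need reconciling. It does not rescue the plan: step 3 shows that change scores alone still leave bias and can cost power.

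**Non-randomization is already conceded.** The Discussion lists it as a limitation, and the bias in step 2 is one form of that confounding. True, but acknowledging a limitation does not reduce it, and this part can be reduced with data in hand.

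**The sizes are assumed.** They are. Nothing in the documents suggests 10% against 30% at the floor, or any particular imbalance. With small imbalances the error rate is close to 5%.

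**Multiplicity.** A reader might count four scales at three visits as 12 tests and compute 1 − 0.95¹² = 46% for at least one false positive. The documents do not support that figure. It needs independent tests, while these are repeated, related scales in the same patients. The protocol ties its level and power to shunt failure, and how secondary outcomes are ordered is commonly left to an analysis plan. I make no point of it.

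**Conclusion.** The point holds in this form: the tests named for the secondary outcomes do not adjust for pre-surgery scores that are collected, in groups that are not randomized; the sections disagree on whether the measure is a score or an improvement; and the favorable outcome is closed to patients entering at NIHSS 0 or 1, whom eligibility does not exclude.

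This is not a detail left to an unseen analysis plan, because the article itself fixes the tests and the responder definition.

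The size cannot be found from the documents. Over the assumed inputs, false positives on a scale run from about 6% to 29%. On the favorable outcome, with 75 per group, they run from about 5% (equal shares at the floor) to 25% (10% vs 30%). The floor argument also takes the NIHSS as an integer scale starting at 0, which the documents do not state. Only secondary outcomes are affected; the primary comparison and its sample size are untouched by this point.

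**What to change.** 1. In sections 2.13 and 2.16 and the Discussion, state one definition of each secondary outcome, and name the pre-surgery score as the reference for NIHSS improvement.
2. In section 2.16, analyze each scale with a model adjusted for its pre-surgery value: ANCOVA or a mixed model over the visits, and an ordinal model for mRS.
3. Analyze the favorable outcome in all patients with adjustment for baseline NIHSS. Add a sensitivity analysis in patients with baseline NIHSS of at least 2, since a smooth baseline term does not reproduce a response probability of exactly zero at 0–1. Report how many in each group enter at 0–1.
4. State that adjusting for the pre-surgery score does not remove confounding by other factors.

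The cost is analysis wording, settled before group comparisons are seen. No visit, measurement or patient is added, because the pre-surgery scores are already scheduled. The sensitivity analysis has a smaller denominator. Keeping all patients in the main analysis avoids changing the endpoint's population, which a restriction to NIHSS of at least 2 would do.

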### Study design

2.2

The Shunting Outcomes of Post-hemorrhagic Hydrocephalus: Phase I (SOPH-1) is a monocentric, assessor-blinded, non-randomized controlled trial. 75 eligible participants for each group would be recruited. Neurosurgeons with extensive experience in the procedure conduct both types of shunt implantation. Each participant is evaluated before surgery, at the time of discharge, 3, and 6 months after surgery by experienced and practiced assessors. The primary outcome is the rate of shunt failure 6 months after shunt surgery. The secondary measure of efficacy is National Institute of Health stroke scale (NIHSS), together along with Glasgow coma scale (GCS), modified Rankin Scale (mRS), and Evans index at the evaluation point. A favorable outcome is defined as shunt success with an improvement of more than 1 point in the (NIHSS). Complication events occurring within 6 months after surgery are investigated. A serious adverse events (SAEs) throughout the study are recorded regarding the safety of shunts.

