### Randomizing and blinding

2.7

Given consent for participation and met eligibility, patients would be assigned groups. The assignment will be performed according to self-selection or administrator selection rather than through randomization and is kept secret by the statisticians who are independent of this study. It is not possible to blind participants to allocation, but data collection teams and analysts are blind to allocation and the intervention clinicians will not participate in any assessment.

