### Primary outcome

2.12

The primary outcome is the rate of shunt failure 6 months after shunt surgery. According to previous study, shunt failure is defined as the occurrence of clinical or radiological signs of shunt obstruction, breakage, tubing exposure, malfunction, or infection requiring shunt revision. Shunt success is defined as the absence of shunt failure.

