On the other hand, it is generally accepted that low-pressure, negative-pressure, and high-pressure hydrocephalus, are not suitable for the LPS implantation. However, the acceptance is not evidence-based. Normal-pressure hydrocephalus is defined as the CSF opening pressure in the range of 70 to 245 mm H_2_O measured by lumbar puncture in the lateral recumbent position according to the Western INPH guideline, comparing to a CSF opening pressure under 200 mm H_2_O based on Japanese INPH guideline.^[21,22]^ Taken together, a range of 70 to 200 mm H_2_O is considered in this study since pressures that are dramatically higher or lower than this range are not suitable for the upcoming LPS implantation.

The current study, however, still has some limitations. First, it is single-center and non-randomized study. Second, medical conditions and surgeons’ experiences are contributed to the postoperative outcomes. In this regard, personnel will be trained centrally in advance and reach uniform standard.

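### Shunt type is assigned by choice, yet only unadjusted tests are planned, so the crude 6-month failure difference cannot separate a shunt effect from selection

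*Protocol article*

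**What the plan says.** Section 2.2 (Study design) states that the study "is a monocentric, assessor-blinded, non-randomized controlled trial". Section 2.7 (Randomizing and blinding) gives the mechanism: "The assignment will be performed according to self-selection or administrator selection rather than through randomization". Section 2.12 defines the endpoint: "The primary outcome is the rate of shunt failure 6 months after shunt surgery".

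Section 2.16 (Statistics analysis) lists the between-group methods:

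- Categorical data, which include the failure rate: "Chi-squared test is used to compare the 2 groups on categorical variables", with Fisher's exact test where appropriate.
- Normally distributed data: "to compare the difference between the 2 groups, independent samples" t-test.
- Non-normal data: "Wilcoxon rank sum test is used".
- Shunt-success curves: Kaplan–Meier, where "log-rank test is used to compare the difference between the 2 groups".

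The article names no regression, matching, weighting, stratification or covariate list. Among the limitations, the Discussion says "First, it is single-center and non-randomized study" and attaches no analytic response to it.

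**The concern.** Each listed test measures the observed difference between two groups. That difference can be read as the effect of the shunt only if the groups would otherwise have had the same failure risk. Randomization would justify that on average. Choice by the patient or an administrator does not.

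The primary conclusion is at stake. If patients at higher risk of failure are more common in one group, the crude comparison can show a difference that the shunts did not cause, or hide one that they did. The P value reflects sampling error only, and recruiting more patients does not remove the bias. The stakes rise because the Discussion twice calls the study a randomized controlled trial and expects it to provide evidence on optimal treatment. That is a causal reading of the crude result, and it conflicts with sections 2.2 and 2.7.

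**Working it through.** **The plan's own figure.** Inputs from section 2.6: failure 15% (VPS) and 35% (LPS), two-sided 5%, power 80%. With unpooled variance,

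n = (1.960 + 0.842)² × [0.15×0.85 + 0.35×0.65] / 0.20² = 7.849 × 0.355 / 0.04 = 69.66, so 70 per group.

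This reproduces the stated 70, which the protocol enlarges to 75. It is a calculation for a crude two-group comparison, with no allowance for adjustment.

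**Illustrations with no true shunt effect.** The documents give neither the strength nor the imbalance of any confounder, so both are assumed here. Let one binary factor raise failure risk from r0 to r1, and let a share a of a group carry it. That group's crude failure rate is a×r1 + (1−a)×r0. Rejection probabilities come from exact enumeration of two binomials, 75 per group, Pearson chi-squared, two-sided 5%.

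| r0 → r1 | Carried by | Crude rates | Spurious difference | Rejection |
|---|---|---|---|---|
| 15% → 35% | 50% vs 50% | 25% vs 25% | 0 points | 4.9% |
| 15% → 35% | 40% vs 60% | 23% vs 27% | 4 points | 8.6% |
| 15% → 35% | 30% vs 60% | 21% vs 27% | 6 points | 13.6% |
| 15% → 45% | 25% vs 65% | 22.5% vs 34.5% | 12 points | 36.8% |

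For example, the third row is 0.30×35% + 0.70×15% = 21% and 0.60×35% + 0.40×15% = 27%.

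**Masking.** At 75 per group, 15% versus 35% gives 81.9% power by the same method. If confounding shrinks the observed gap by 6 points, to 18% versus 32%, power is 51.0%.

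**Room for adjustment.** Expected failures are 75×0.15 + 75×0.35 = 37.5. At the customary 10 per term (a rule of thumb), an outcome model carries 3 to 4 terms. A propensity model is limited by the smaller treatment group: 75/10 = 7.5, so about 7. Age (1), hemorrhage type (three categories in section 2.4, so 2), opening pressure (1) and Evans index (1) make 5. One or two of NIHSS, GCS and mRS bring this to 6 or 7. Entering all three would make 8, and adding date of surgery 9, which exceeds the limit.

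**Cost in power.** From 70 evaluable per group, a 10% loss of effective sample size leaves 63 and a 20% loss leaves 56. Power for 15% versus 35% is then 79.7%, 75.0% and 70.1% in turn.

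**The case against.** Several points on the other side are fair.

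- **Eligibility already restricts the comparison.** Sections 2.4 and 2.5 require non-obstructive hydrocephalus, shown communication with the spinal space and an opening pressure of 70–200 mmH2O in both groups. This removes some reasons for preferring one shunt. It does not balance age, severity or hemorrhage type among those enrolled.
- **The text does not say that choice follows prognosis.** A reader might infer that patients are steered to a shunt by severity, so that the result is certainly confounded by indication. Section 2.7 says only who chooses, not on what grounds. What stands is that confounding cannot be excluded.
- **The baseline values are not shown to predict failure.** A reader might take them as strong prognostic factors. Failure in section 2.12 means obstruction, breakage, exposure, malfunction or infection requiring revision, and nothing in the article links these to NIHSS or GCS. They are candidate covariates only.
- **The training measure.** A reader might take central training as the answer offered to non-randomization. In the Discussion it answers the second limitation, on medical conditions and surgeons' experience.
- **The magnitudes are assumed.** The 37% case needs a factor that triples failure and a 40-point gap in who carries it. A milder imbalance gives about 9%.
- **An analysis plan may exist.** Covariate lists and sensitivity analyses often sit there, and section 2.16 does not exclude adjusted analyses. But it does state the between-group tests, and those do not suit a comparison formed by choice. That mismatch is in the protocol itself.

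Assessor blinding does not help here, since it guards against biased assessment and not against selection.

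**Conclusion.** The point holds in this form: the stated methods do not fit the stated design, and the crude 6-month failure difference cannot separate a shunt effect from selection. It rests on two explicit statements, assignment by choice in section 2.7 and only unadjusted tests in section 2.16. The protocol admits non-randomization but offers no analytic remedy.

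How far, and in which direction, the result would be biased cannot be known from the documents. Under the assumed single-factor scenarios, the nominal 5% error becomes roughly 9% to 37%, with spurious differences of 4 to 12 points against a design difference of 20. These are illustrations, not estimates for this trial. The stronger claim, that the primary result will be confounded by indication, is not supported.

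**What to change.** In section 2.16, make the primary estimate a pre-specified adjusted 6-month risk difference (VPS minus LPS) with a 95% confidence interval. Propensity-score weighting is one suitable method; matching or a parsimonious regression would also serve. If overlap weighting is used, state its target population, because it describes patients who could plausibly have received either shunt.

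Name the covariates before outcomes are seen, with no more than about 7 degrees of freedom: age, hemorrhage type, opening pressure, Evans index, and one or two of NIHSS, GCS and mRS. Hemorrhage type, opening pressure and Evans index are established at eligibility. Section 2.2 provides for an evaluation before surgery, and the favorable-outcome definition needs a starting NIHSS. The schedule table is not visible in the text reviewed, so the pre-surgery timing of GCS and mRS should be confirmed.

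Report covariate balance before and after adjustment. Keep the crude chi-squared and log-rank tests as supportive. Word the conclusions to allow for unmeasured confounding, which no adjustment removes, and correct the two descriptions of the study as randomized in the Discussion.

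The cost is some additional analysis work, including a check that the chosen method is practical in the SPSS version named, and some loss of effective sample size. The protocol should state the resulting power: about 75–70% for a 10–20% loss at 70 evaluable per group. No new patients or measurements appear to be needed, unless the sponsor wishes to restore 80% power.
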